**Objectives:**

This study aims to investigate the therapeutic potential of smoking cessation for individuals with SUD, using a Cognitive-Behavioral Therapy (CBT) six-week group intervention within a therapeutic community. The research specifically explores the psychobehavioral, metabolic, and gut microbiome domains. It is hypothesized that smoking cessation will improve emotional regulation self-efficacy and reduce substance craving, mediated by changes in metabolic and microbiome profiles linked to brain systems of affect and reward.

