#### Gut microbial domain

2.1.3

In line with previous studies, we hypothesize that smoking contributes to gut microbial imbalances, reduced general bacterial diversity and abundance of commensals, and growth of pathogens (91). We hypothesize that reversed effects in these imbalances will be observable after smoking cessation. Further emphasis will be put on the identification of microbial markers corresponding with general substance craving, history of smoking and success of smoking cessation. Gut microbial correlates of primary emotions and psychiatric symptoms will be identified in exploratory analyses. Analyses will further focus on bacterial genera with a known role (as derived from literature) in the metabolism of SCFA, PUFA, bile acids, and tryptophan (metabolites) (20). Combined metabolome-microbiome analyses will ascertain associations between bacterial abundances and concentrations of relevant metabolites.

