### Innovative aspects of the therapeutic community approach for SUD

3.2

The immanent assumption of the therapeutic community approach (36) is that SUD reflects deeper disturbances in identity and personality structure, values, emotional regulation, and social functioning rather than being only a biomedical dependency. Therefore, the central mechanism of change is “community as method,” meaning that recovery occurs primarily through structured social living, mutual self-help, and social learning processes in which peers provide feedback, role modeling, accountability, and reinforcement of pro-social behavior. The practical approach in a SUD recovery institution – which represents the actual environment for participants of the present study – goes along with structured leisure, work and community activities, as well as meals and exercise. This structure might contribute to social learning and establishing daily routines, a sense of goal-directedness and motivation for sustained drug abstinence (36). But it is also in harmony with metabolic and nutritional psychiatry (93), and microbiome perspectives, as it can be hypothesized that this structured way of life supports the restoration of circadian rhythms, metabolic and gut microbial homeostasis, and normalization of reward circuitry (96, 97).

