### Type and design of the study

4.1

The present study is a randomized controlled experiment in N = 100 SUD- inpatients during a therapeutic community treatment with one intervention group that will receive an additional 6-week smoking cessation intervention and one control group that will receive treatment as usual. The study design consists of a 2 x 2 mixed subject design with repeated measures for the biological analyses and a 2 x 3 mixed subject design with repeated measures for the psychobehavioural analyses (see **Table 1**). In both groups, an examination of metabolic and gut microbial profiles, as well as psychological variables, will take place. Biological parameters will be ascertained from blood and stool specimens for nuclear magnetic resonance (NMR) spectroscopy metabolomic analyses and from stool specimens for 16s-mRNA (hypervariable V3-V4 regions) sequencing and subsequent gut microbial profiling. Psychobehavioural and biological data will be collected pre & post smoking cessation, and additionally, there will be a follow-up measurement of the psychobehavioural variables 3 months upon completion of the study (see **Figure 3**: Consort Flow Chart for further illustration).

**Table 1 T1:** Overview of the statistical design.

Study group	Pre- intervention baseline	Post- intervention after 6 weeks	Follow- up after 3 months
Intervention Group (N = 50)	Psychobehavioural Data	Psychobehavioural Data	Psychobehavioural Data
	Metabolic/Microbial Data	Metabolic/Microbial Data	
Control Group (N = 50)	Psychobehavioural Data	Psychobehavioural Data	Psychobehavioural Data
	Metabolic/Microbial Data	Metabolic/Microbial Data	

green cells: biological data; light brown cells: self-report data.

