#### Controlling for potentially confounding variables, and multiple testing

4.7.3

Proper analysis of the research questions in the SUD sample will be hampered by several sources of variance, such as diet, psychiatric diagnoses, medications, and history of substance misuse. These variables will be held constant as control variables.

Psychiatric comorbidity is highly present in the population. Psychiatric symptom burden and classes of psychiatric diagnoses are associated with systematic metabolic and microbiome profiles (72, 113, 114). Classes of psychiatric secondary diagnoses (mood, anxiety, psychotic, and neurodevelopmental disorders) will therefore be considered as covariates. Intake of psychotropic medications are respectively frequent. The literature shows reciprocal interactions between psychotropic medications and gut microbiota (115), and metabolic patterns in response to treatment (116, 117). Type of medication class intake (antipsychotics, antidepressants, antianxiety drugs, anticonvulsants/mood stabilisers, opioid substitution) will be considered as covariates. Length and consumption patterns from SUD history will also enter covariate analysis (with regard to substances – primarily consumed substances vs. polytoxicomania). These covariates will be entered in Multi-omics factor analysis (MOFA) in direct joint modeling (118) to ensure that observed microbiome–metabolome–psychological associations are not driven by covariate effects. For the microbiome domain, intervention vs. control group comparisons regarding microbial abundance and composition will be performed with Analysis of Compositions of Microbiomes with Bias Correction (ANCOM-BC), a package which allows for continuous and categorical covariate adjustment within a linear regression framework, and was designed to analyze longitudinal data (119).

Metabolome and microbiome studies involve the examination and statistical testing of a multitude of variables. Thus, controlling for multiple testing is a must; False Discovery Rate corrections will be based on statistical recommendations promoting flexible algorithms within the R package FDRestimation (120).

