#### Statistical analyses of psychological variables

4.7.4

The statistical analyses will be performed in SPSS version 29 (IBM) for general procedures, while specific regression models are handled in R (R core team (121)). For example, t-tests will be carried out for independent and paired comparisons of means between and within groups at different times, respectively, assuming that the continuous data are normally distributed. Chi-square and Fisher’s exact tests, the latter in cases of smaller sample sizes, will be conducted in order to test the associations between categorical variables. The Friedman test shall be used in analyzing non-parametric repeated measures. The main effects of the intervention, time effects, and group x time interaction will be tested using a 2 × 3 two-way repeated measures ANOVA design (group x time), using the Greenhouse-Geisser correction in cases when the sphericity assumption will be violated. The level of significance will be α = 0.05, two-tailed, using Bonferroni adjustment for multiple comparisons. In addition, a repeated measures proportional odds logistic regression model using a generalized estimating equation (GEE) will be applied, assessing the intervention’s effect on CPD treated as an ordinal variable. The GEE model, computed in R using the `repolr` package (122), will contain robust variance estimators that take into account within-subject correlations (**Table 2**).

**Table 2 T2:** Summary of statistical methods and outcomes.

Outcome variable	Domain	Statistical method	Software
Self-efficacy, craving, psychiatric scores	Psychobehavioural	Repeated measures ANOVA, t-tests, Friedman test	SPSS
Cigarettes per day (ordinal)	Psychobehavioural	GEE (Proportional odds model)	R (repolr)
Bacterial diversity indices	Microbiome	Kruskal-Wallis, ANOSIM, db-RDA	R, QIIME
Taxonomic composition	Microbiome	MaAsLin2, ANCOM, LEfSe	QIIME2, R
Metabolite concentrations	Metabolic	PCA, O-PLS-DA, correlation analyses	NMR tools, R
Cross-domain associations	Combined (exploratory)	Correlation and regression	R

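### The covariate set meant to protect the exploratory cross-domain associations names neither randomised arm nor visit, the two factors the plan itself expects to shift all three domains

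*Protocol article*

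**What the plan says.** Table 2 (section 4.7.4) summarises the method for cross-domain associations as "Correlation and regression" and marks the row exploratory. Section 2.1.3 describes the purpose of the combined analysis: "Combined metabolome-microbiome analyses will ascertain associations between bacterial abundances and concentrations of relevant metabolites".

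Section 4.7.3 is where the plan protects these associations. It identifies "several sources of variance, such as diet, psychiatric diagnoses, medications, and history of substance misuse", then spells out diagnosis classes, medication classes and consumption history. It continues: "These covariates will be entered in Multi-omics factor analysis (MOFA) in direct joint modeling", with the aim "to ensure that observed microbiome–metabolome–psychological associations are not driven by covariate effects". Section 8 adds sex. Section 4.7.5 also plans MaAsLin2 tests of taxa against metabolic markers and gives no arm or visit term for them.

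Group does appear elsewhere, where a group effect is itself the target: the variance decomposition and mixed models in 4.7.2, ANCOM-BC in 4.7.3 and 4.7.5, and the ANOVA in 4.7.4. Biological data are collected in both arms at two visits (section 4.1: "2 x 2 mixed subject design with repeated measures for the biological analyses").

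**The concern.** By the plan's own hypotheses, arm and time are common causes. Sections 2.1.1 to 2.1.3 expect the cessation programme to change scores, metabolites and microbiota. Section 3.2 expects community life, which both arms share, to act over time as well: "this structured way of life supports the restoration of circadian rhythms, metabolic and gut microbial homeostasis". Two measures that are independent within each arm and visit become correlated when arms or visits are combined without a term for them.

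The objectives in the abstract hypothesise that the benefit of cessation is "mediated by changes in metabolic and microbiome profiles linked to brain systems of affect and reward". A link between mediator and outcome has to be estimated conditional on treatment. Otherwise two parallel, unconnected effects of the programme can be read as a mechanism. FDR control does not remove this, because the combined-arm correlation really is non-zero; it simply does not show that one measure is linked to the other. The more the programme changes, the more such pairs appear.

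**Working it through.** The article states no figure for the cross-domain analysis, so there is none to reproduce. The question is how large the induced correlation could be.

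**Inputs**
- Planning effects (4.7.1): metabolite d = 0.73; taxon r = 0.41; self-efficacy d = 0.70.
- Converting the taxon effect: d = 2 × 0.41 / √(1 − 0.41²) = 0.82 / 0.912 = 0.90.
- Completers: 50 per arm less about 10% attrition (4.7.1) = 45 per arm, n = 90.
- Assumptions: no link within arm; equal arms; two-sided 5% test without correction.

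**Induced correlation, arms combined, one visit**

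r = (d₁d₂/4) / √[(1 + d₁²/4)(1 + d₂²/4)]

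Metabolite and self-efficacy: (0.73 × 0.70 / 4) / √(1.133 × 1.1225) = 0.1278 / 1.128 = 0.113. Rejection rates follow from Fisher's z with standard error 1/√87. Simulation (10,000 trials per row) gave the last two columns.

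| Arm effects (SD) | r | Rejection, Fisher z | Simulated, no arm term | Simulated, arm term |
|---|---|---|---|---|
| 0.73, 0.70 | 0.113 | 18.6% | 18.6% | 5.5% |
| 0.70, 0.90 | 0.136 | 24.6% | 25.3% | 4.9% |
| 0.73, 0.90 | 0.141 | 26.2% | 27.3% | 5.0% |
| 0.4, 0.4 | 0.038 | 6.5% | 6.5% | 5.2% |
| 0.4, 0.5 | 0.048 | 7.3% | 7.4% | 5.3% |
| 0.5, 0.5 | 0.059 | 8.5% | 8.9% | 5.2% |

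Change scores behave like the single visit when the within-person correlation is 0.5: with d = 0.73 and 0.70 at 50 per arm, rejection was 19.7% for post-intervention values and 20.9% for change.

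**If both visits were pooled as independent rows (not stated in the article)**

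With d = 0.73 and 0.70 at 50 per arm, r = 0.087 and rejection is about 25%. Part of that comes from ignoring repeated measures: with no effects at all, the rate was already 7.5%. Adding an assumed 0.5 SD shift over time in both arms gives r = 0.20 and about 82%.

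**Does an arm term remove the whole shared effect?**

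It does when the shared cause is arm, as in the table. If the shared cause is quitting, which varies within arm, it does not. Assume 54% quit in the intervention arm (14 of 26 quit in the microbiome study cited in 4.7.1) and 10% in control, with the planning effects applied to quitters.
- Total variance of quitting: 0.32 × 0.68 = 0.2176.
- Mean within-arm variance: (0.54 × 0.46 + 0.10 × 0.90) / 2 = 0.1692.
- For d = 0.73 and 0.70, unadjusted: r = 0.511 × 0.2176 / √[(1 + 0.533 × 0.2176)(1 + 0.49 × 0.2176)] = 0.100, rejection about 15%.
- Arm-adjusted, with 0.1692 in place of 0.2176: r = 0.080, rejection about 11%.
- Across the three pairs: about 15 to 22% unadjusted and 11 to 15% with arm. Adding quit status brings it to about 5%.

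**The case against.** The strongest reply is that this treats a summary as a specification. Table 2 is a short overview, the row is labelled exploratory, and a regression can contain arm. Nowhere does the article say that arms or visits are pooled or that arm is left out. Section 4.7.3 concerns confounders and introduces them as examples; randomised arm is the exposure, and 4.7.2 keeps group apart from control variables. A fuller plan may supply the terms. Much of this stands. A reader might infer that the plan commits to pooled, unadjusted correlations, and the text does not support that. What remains is narrower: the article does fix a covariate set, says what it is for, and leaves out two factors its own hypotheses make common causes.

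Nor is simple correlation the whole plan, since MOFA and MaAsLin2 are also foreseen. They do not settle the matter, because neither arm nor visit is named for them in this role.

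The size is also open to challenge. The metabolite figure compares smokers with former smokers, and the taxon figure compares quitters with continuing smokers; neither is an arm difference. Under the quit rates assumed above, they shrink to 0.44 × 0.73 = 0.32 and 0.44 × 0.90 = 0.40. The rates shown are before FDR correction: at r of 0.11 to 0.14, rejection is about 7 to 11% at p < 0.01 and 1 to 2% at p < 0.001. Both points stand, so the 18 to 27% range is an upper case.

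**Conclusion.** The point holds in a limited form. The covariate set given for the exploratory cross-domain analyses does not name arm or visit, so as written it does not secure its stated aim. If arms are combined without an arm term, unlinked measures show r of about 0.11 to 0.14 and about 18 to 27% rejection at 5% when the planning effects are read as arm differences. At arm effects of 0.4 to 0.5 SD the excess is slight: 6 to 7%, or about 9% with both effects at 0.5. All figures assume 45 per arm and no true link within arm.

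Two stronger conclusions are not supported. A reader might take the figure of about 82% as the expected error rate, but it needs pooled visits and a 0.5 SD common shift; the article states neither, and section 3.2 gives no size. A reader might also conclude that adding arm cures the problem. It does so only where arm is the sole shared cause; with quitting as the shared cause, about 11 to 15% rejection remains under the assumed quit rates.

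**What to change.** In Table 2 and section 4.7.3, state that cross-domain associations are estimated on within-person change (week 6 minus baseline), by partial correlation or regression with arm as a term beside the listed covariates. If both visits are modelled instead, include arm, visit and a subject effect. Apply the same terms to the MaAsLin2 tests against metabolic markers in 4.7.5. Report baseline associations separately.

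Add a sensitivity analysis that also adjusts for abstinence, using the two-week abstinence item in section 4.4.1. Abstinence is measured after randomisation, so this belongs beside the arm-adjusted result and should not replace it.

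For MOFA, report how the fitted factors relate to arm and visit. Regressing these out beforehand need not be required, since it would also remove programme-driven variation that the study wants to describe.

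The cost is wording and one or two degrees of freedom per model, with no new data.

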#### Microbiome analyses

4.7.5

One gram of collected stool sample will be immediately stored in a -80 °C-freezer. Sequence analysis will be done according to the supplier’s recommendations. The workflow for microbiome analysis with Illumina MiSeq has already been described in detail in Klymiuk et al. (123). The Magna Pure LC DNA III Isolation Kit (Bacteria) (Roche, Mannheim, Germany) will be used to extract DNA according to manufacturer’s instructions. The hypervariable V3–V4 regions of the bacterial 16S rRNA gene will be amplified with Polymerase-chain-reaction (PCR) from total fecal DNA using the target-specific primers. 2µl of total DNA will be used in a 25µl PCR reaction in triplicates with the FastStart High Fidelity PCR system (Sigma, Germany). Cycling condition of initial denaturations at 95 °C for 3 minutes, followed by 30 cycles of 95 °C for 45 sec, 55 °C for 45 sec, 72 °C for one minute and a final elongation step at 72 °C for seven minutes. The resulting amplification products will be visualized on a 1.5% agarose gel and pooled, indexed and purified as described in Klymiuk et al. (123). The final library will be sequenced at ZMF Core Facility Molecular Biology in Graz, Austria, using an Illumina MiSeq desktop sequencer with v3 chemistry and 600 cycles (2x300). Unmapped bam files will be used as input for bioinformatics. To analyze the microbial community structure and taxonomic diversity, the obtained raw reads will be processed using Quantitative Insights Into Microbial Ecology (QIIME) scripts. During processing in silico, the FASTQ files will be paired, demultiplexed, dereplicated, and quality controlled. Further processing will include the use of the DADA2 algorithm (124) for sequence inference and chimera removal. Low-abundance features will be removed below a threshold of 20 total counts and presence in less than 5 samples. Sequences will be aligned against the SILVA 132 database, using the Scikit-learn classifier for taxonomic identification. The MAFFT software will be employed for *de novo* multiple alignment; the resulting alignment will be further treated with FastTree for phylogenetic tree construction (125). The Pielou’s Evenness Index considers species evenness and is similar to the Shannon-Wiener diversity model. Besides, Faith’s Phylogenetic Diversity (PD) accounts for phylogenetic differences among species. Numbers of detected species will be used for approximating richness, and Shannon Index for overall diversity estimates. Analyses of alpha diversity will be done in R (4.2) and RStudio. The pairwise Kruskal-Wallis test will be used to make statistical comparisons between the smoking cessation intervention and control groups.

For beta diversity, db-RDA will be performed on Bray-Curtis, Jaccard, and UniFrac distance matrices (weighted and unweighted) to compare the structural similarities between groups’ microbiomes. Beta diversity indices will be visualized with PCoA plots using Bray-Curtis and Jaccard dissimilarities. The Firmicutes/Bacteroidetes (F/B) ratio will be calculated from the rarefied feature table. Using this, MaAsLin2 will be used to detect differentially abundant taxa and further test associations with variables of interest such as cigarettes per day or metabolic markers (126). Identifications of microbial biomarkers will then be done applying LeFSe both in longitudinal and cross-sectional comparisons. This will be furthered to detect significant differences between groups in the microbial taxonomic abundance using the Analysis of Composition of Microbiomes’ ANCOM-BC implemented within QIIME2 (119).

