A-priori sample size calculations were performed with G-Power (108) (version 3.1.9.6), for a mixed-design ANOVA with one interaction between group (2 groups) and assessments (2 repeated measurements). Considering the effects mentioned above, the mixed-design ANOVA was set rather conservatively for a medium effect size (Cohen’s F = 0.25), a statistical Power (1-β) of 0.9, a α of 0.05, an intra-correlation coefficient of 0.5 and nonsphericity correction of 1, resulting in a minimum sample size of 46 subjects per group, and a critical F = 4.06. Adjusting for expected attrition of about 10%, a total sample size of size of 100 is set. The many (mostly biological) variables measured in this study will expectably require statistical corrections; this will also be compensated by statistical methods exceeding classical linear approaches, namely machine learning feature detection and modelling methods (109).

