##### NMR analysis of plasma metabolites

4.7.6.3

Blood plasma low molecular weight metabolites and lipoproteins will be also be analyzed on a Bruker 600 MHz Avance Neo NMR spectrometer. Plasma samples will be thawed, and 330 μl of each sample will be mixed with 330 μl of Bruker plasma buffer (Bruker, Rheinstetten, Germany). Following gentle mixing, 600 μl of the samples will be transferred into 5mm glass tubes and placed into a SampleJet rack (Bruker, Rheinstetten, Germany). Proton spectra will be ascertained at a temperature of 310 K using a standard nuclear Overhauser effect spectroscopy (NOESY) pulse sequence (Bruker: noesygppr1d), a Carr–Purcell Meiboom–Gill (CPMG) pulse sequence with pre-saturation during the relaxation delay (Bruker: cpmgpr1d) to achieve water suppression, and a fast scan 2D J-resolved (JRES) pulse sequence (Bruker: jresgpprqf). Data analyses will be carried out using Bruker IVDr Plasma (B.I.) module of the analysis software (Topspin version 4.1). Univariate statistical analysis of the concentration values for identifying lipoproteins and metabolites of interest differing between groups will again be carried out using MetaboAnalyst and the R package rstatix.

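### Alpha-diversity and metabolite tests are named only as between-group comparisons with no baseline, time or participant term, although the biological design and sample size rest on group x time

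*Protocol article*

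**What the plan says.** Section 4.1 sets the frame: "The study design consists of a 2 x 2 mixed subject design with repeated measures for the biological analyses". Blood and stool are taken before and after the intervention. The sample size in section 4.7.1 was computed "for a mixed-design ANOVA with one interaction between group (2 groups) and assessments (2 repeated measurements", with "a statistical Power (1-β) of 0.9, a α of 0.05, an intra-correlation coefficient of 0.5 and nonsphericity correction of 1". The hypotheses in sections 2.1.2 and 2.1.3 concern change: choline rises, and microbial imbalances reverse, after cessation.

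The biological tests are named as follows.

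- **Alpha diversity** (4.7.5): "The pairwise Kruskal-Wallis test will be used to make statistical comparisons between the smoking cessation intervention and control groups".
- **Metabolites** (Table 2, in 4.7.4): "PCA, O-PLS-DA, correlation analyses". For plasma, 4.7.6.3 adds "Univariate statistical analysis of the concentration values for identifying lipoproteins and metabolites of interest differing between groups".
- **Beta diversity** (4.7.5 and Table 2): ANOSIM and db-RDA between groups.
- **Taxa** (4.7.5): MaAsLin2, ANCOM-BC and LEfSe. On the last, "Identifications of microbial biomarkers will then be done applying LeFSe both in longitudinal and cross-sectional comparisons".
- **Candidate biomarkers** (4.7.2): lme4 mixed models, with and without nutrition terms, fitted to metabolites or taxa that the preceding analyses have already picked out.

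By contrast, section 4.7.4 gives the psychobehavioural outcomes an explicit group x time ANOVA, and gives cigarettes per day a GEE that allows for within-person correlation.

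**The concern.** The design collects a baseline sample from everyone so that change can be compared between arms, and the sample size assumes such a comparison. For alpha diversity and metabolites, the named tests do not make it. Kruskal-Wallis takes one grouping factor and no covariate, and O-PLS-DA and the univariate comparisons are described only as separating groups.

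The mixed models in 4.7.2 do not repair this, because a metabolite that the screening test misses never reaches them. ANCOM-BC and MaAsLin2 deal with taxa, not with diversity indices or metabolites.

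At stake is power in two of the study's three domains, and whether the reported tests answer the stated hypotheses about change. Longitudinal LEfSe is a separate weakness: it screens features with an independent-samples rank test, while pre and post samples from one person are paired.

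**Working it through.** **Inputs.** From section 4.7.1: correlation rho = 0.5, alpha = 0.05, f = 0.25, about 10% attrition. From Table 1: 50 per arm, so 50 x 0.9 = 45 completers per arm. Assumed, because the article gives no figure: a true week-6 difference of 0.5 SD (0.7 SD as an alternative) and rho of 0.3 or 0.7 as a range. All powers are per test at 0.05, before FDR.

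**The plan's own figure.** For the group x time interaction, lambda = f² x N x m/(1 - rho). With a total N of 46 and m = 2 visits, lambda = 0.0625 x 46 x 2/0.5 = 11.5, critical F(1,44) = 4.06 and power 0.912. The stated critical F of 4.06 therefore belongs to 46 participants in total. At 46 per group it would be F(1,90) = 3.95, with power 0.997. That label is a separate matter. Here it confirms that the powered test is the interaction.

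**Power to detect a difference between arms.** Relative variance of each estimator, in units of 2 x SD²/n:

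- week-6 value only: 1 (a rank test has efficiency 0.955 relative to the t test)
- change score, equivalent to group x time: 2(1 - rho)
- baseline-adjusted (ANCOVA): 1 - rho²

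Noncentrality is 0.5/sqrt(2 x factor/45). At rho = 0.5 this is 0.5/sqrt(2/45) = 2.37 for week 6 only and 0.5/sqrt(2 x 0.75/45) = 2.74 for ANCOVA. Powers with 45 per arm:

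| Effect, rho | Week-6 t test | Week-6 Kruskal-Wallis | Change score | Baseline-adjusted |
|---|---|---|---|---|
| 0.5 SD, 0.3 | 0.65 | 0.63 | 0.51 | 0.69 |
| 0.5 SD, 0.5 | 0.65 | 0.63 | 0.65 | 0.77 |
| 0.5 SD, 0.7 | 0.65 | 0.63 | 0.86 | 0.91 |
| 0.7 SD, 0.5 | 0.91 | 0.89 | 0.91 | 0.97 |

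Put as sample size at rho = 0.5, a week-6 t test would need 45/0.75 = 60 completers per arm to match ANCOVA with 45.

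A Kruskal-Wallis test on change scores would use the baseline, but the text does not say this. At rho = 0.5 it would gain nothing over week 6 alone, since 2(1 - 0.5) = 1.

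**Longitudinal LEfSe, if run unpaired pre versus post.** The test assumes a variance of 2 x SD²/n for the mean difference, while the true variance is 2(1 - rho) x SD²/n. The actual alpha is 2 x (1 - Phi(1.96/sqrt(1 - rho))). At rho = 0.5 this is 2 x (1 - Phi(2.77)), about 0.006 instead of 0.05.

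**The case against.** A fair defence runs as follows.

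- With one week-6 sample per person, the arms are independent. Under randomisation the week-6 difference has the same expectation as the group x time contrast, so the Kruskal-Wallis test is valid. This stands.
- Measured against the interaction on which the trial is powered, the loss at rho = 0.5 is only about 0.02 (0.63 against 0.65), and at rho = 0.3 week 6 alone does better. This stands too. The gain comes from baseline adjustment, not from the interaction as such.
- The 0.5 SD effect is an assumption. Section 4.7.1 cites effects near 0.7, where the gap is 0.89 to 0.97. Under the formula that reproduces the critical F, f = 0.25 is a 1.0 SD difference in change (four cells displaced by 0.25 SD), where week-6 power exceeds 0.99. The gain thus matters for smaller effects and, because FDR lowers the working threshold, for wide screens.
- The article is condensed and the biological work is declared largely exploratory. Which visit is tested, random effects and permutation schemes may be set in an analysis plan. This explains silence on detail. It does not change the family of test the article names for these outcomes.
- Suitable tools are already listed: ANCOM-BC, described as suited to longitudinal data; partial db-RDA or PERMANOVA for microbial and metabolite distances (4.7.2); and lme4. But none is given a time term or baseline covariate, and none is the main test for a single diversity index or metabolite.

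A reader might infer that both visits will be pooled as independent samples, which would inflate false positives. No section says so, and the wording for alpha diversity describes only a comparison between arms.

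**Conclusion.** The point holds as a mismatch between design and named tests, with a cost in precision. For alpha diversity and metabolites the plan fixes between-group tests that, as described, do not use the baseline. On the favourable week-6 reading, baseline adjustment would raise power from about 0.63 to 0.65 up to 0.77 (45 per arm, assumed 0.5 SD, rho 0.5), or to 0.91 if rho were 0.7. The gain shrinks for larger effects and for lower correlation.

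Longitudinal LEfSe is the weakest single item. The alpha of 0.006 applies only if it is run as an unpaired pre-post comparison, which the text neither states nor rules out.

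A reader might also conclude that the biological comparisons are invalid or do not estimate the randomised effect. The documents do not support that: a week-6 comparison of randomised arms is valid, though inefficient. This is a worthwhile and nearly free improvement, not a flaw that invalidates the trial.

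**What to change.** - **Each diversity index and metabolite:** make the main test a regression of the week-6 value on arm and baseline, transformed if needed, with FDR applied to the arm effect. An arm x time mixed model with a participant random intercept also fits the design. Constrain the baseline means to be equal across arms if it is to match the power of the adjusted model; unconstrained, it behaves like the change score.
- **Beta diversity:** test arm x time by db-RDA or PERMANOVA, with permutations restricted by participant.
- **Taxa:** include a participant random effect in MaAsLin2 whenever both visits enter. Limit LEfSe to a descriptive week-6 comparison.
- **Nutrition adjustment (4.7.2):** select the candidates from these models.
- **Table 2:** update it to match.

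The cost is wording in sections 4.7.2, 4.7.5 and 4.7.6 and in Table 2. No extra samples or visits are needed, and lme4, MaAsLin2, db-RDA and PERMANOVA are already in the plan. The change should be fixed before the biological data are analysed.
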